# Remote Blood Pressure Monitoring With a Wearable Photoplethysmographic Device (Senbiosys): Protocol for a Single-Center Prospective Clinical Trial

**DOI:** 10.2196/30051

**Published:** 2021-10-07

**Keywords:** continuous blood pressure monitoring, photoplethysmography, arterial line, Senbiosys, wearable devices, blood pressure, remote monitoring, continuous monitoring, mHealth, mobile health

## Abstract

**Background:**

Wearable devices can provide user-friendly, accurate, and continuous blood pressure (BP) monitoring to assess patients’ vital signs and achieve remote patient management. Remote BP monitoring can substantially improve BP control. The newest cuffless BP monitoring devices have emerged in patient care using photoplethysmography.

**Objective:**

The Senbiosys trial aims to compare BP measurements of a new device capturing a photoplethysmography signal on the finger versus invasive measurements performed in patients with an arterial catheter in the intensive care unit (ICU) or referred for a coronarography at the Hospital of Fribourg.

**Methods:**

The Senbiosys study is a single-center, single-arm, prospective trial. The study population consists of adult patients undergoing coronarography or patients in the ICU with an arterial catheter in place. This study will enroll 35 adult patients, including 25 patients addressed for a coronarography and 10 patients in the ICU. The primary outcome is the assessment of mean bias (95% CI) for systolic BP, diastolic BP, and mean BP between noninvasive and invasive BP measurements. Secondary outcomes include a reliability index (Qualification Index) for BP epochs and count of qualified epochs.

**Results:**

Patient recruitment started in June 2021. Results are expected to be published by December 2021.

**Conclusions:**

The findings of the Senbiosys trial are expected to improve remote BP monitoring. The diagnosis and treatment of hypertension should benefit from these advancements.

**Trial Registration:**

ClinicalTrials.gov NCT04379986; https://clinicaltrials.gov/ct2/show/NCT04379986

**International Registered Report Identifier (IRRID):**

PRR1-10.2196/30051

## Introduction

Systemic arterial hypertension is a major modifiable cardiovascular risk factor [1]. The 10-year incidence of hypertension in the Swiss population has been estimated to be almost one-third [2]. Many patients with hypertension are aware of their condition but are either untreated or inadequately treated, although effective treatment of hypertension reduces morbidity and mortality rates [3].

Remote blood pressure (BP) monitoring—accompanied by education on hypertension management by caregivers—can substantially improve BP control. Wearable devices can provide user-friendly, accurate, and continuous BP monitoring to assess patient’s vital signs and achieve remote patient management [4-6].

The newest cuffless BP monitoring devices use photoplethysmography (PPG) [6,7]. This method consists of emitting light to the skin through a light-emitting diode and then measuring the changes in light absorption to a photodiode to detect peripheral volumetric variations of blood circulation [8]. A PPG waveform has been proven to correlate well with BP waveforms and truly represents one cardiac cycle, comprising the systolic peak, the diastolic peak, and the dicrotic notch [9,10]. One of the main challenges of this technique is to obtain an accurate estimate from the different PPG morphologies that are affected by patient’s characteristics, including age, vessel stiffness, cardiovascular disease, and other hemodynamic properties [11,12].

The Senbiosys device uses a PPG-based pulse wave analysis technique, which involves morphological analysis of the PPG pulse waveform thanks to an algorithm that identifies combinations of features of the PPG waveform to estimate BP [13,14]. Moreover, the PPG signal quality strongly depends on the body location [15]. In this regard, the Senbiosys PPG technology captures the PPG signal in the finger, which is known to be one of the best locations in terms of signal fidelity. The accuracy of the PPG-based technology is of fundamental importance, and several validation procedures for assessing the precision of BP monitoring devices have been developed [16].

The purpose of this study is to evaluate the accuracy of the Senbiosys device for measuring BP compared to invasive BP measurements with the arterial line, the gold standard in the hospital setting. Participants will undergo invasive BP estimation and will simultaneously wear the Senbiosys device.

## Methods

### Study Setting

This is a single-center, single-arm, prospective trial aiming to assess the accuracy of the Senbiosys device to estimate BP versus the invasive BP measurement. The patients will undergo invasive BP estimation and will simultaneously wear the device. This study will enroll 25 adult patients addressed for a coronarography and 10 patients in the intensive care unit (ICU). The intervention period that the devices are worn is between 10 and 15 minutes for each patient. There is no follow-up period after intervention.

### Inclusion and Exclusion Criteria

All patients 18 years or older either referred for coronarography or in the ICU requiring invasive BP monitoring and with an arterial catheter in place are eligible for the study. A modified Allen test will be routinely performed prior to arterial catheterization as per clinical routine.

The presence of any of the following exclusion criteria will lead to exclusion of the participants:

Patient unable or unwilling to provide written informed consent themselves, which presupposes the patient’s capacity for discernmentCoronarography in patients with myocardial infarctionPatient with suspected or certified COVID-19 infectionPatients with atrial fibrillationPatients with intracardiac monitoringSignificant noninvasive systolic BP (SBP) difference between left arm and right arm (difference >20mmHg in systolic arterial pressure)

### Intervention

The investigated device is the SBF2003, manufactured by Senbiosys, which is a ring measuring the patient’s PPG on the fingers. The intervention period that the devices are worn is between 10 and 15 minutes for each patient. The way the device is worn on a finger is depicted in Figure 1.

**Figure 1 figure1:**
[figure not shown]
SBF2003 and the way the device is worn on a finger during operation.

#### Standardized Measures in the Cardiac Catheterization Laboratory

The investigator will put the ring on the index finger of the patient’s hand. The device will be placed prior to the placement of the sterile field and will not be in contact with it. Arterial puncture will be performed either via the radial or femoral access according to the clinician’s choice. Intra-arterial BP waveforms will be recorded using a fluid-filled catheter. The catheter will be flushed before any waveform recordings are made. At first, the catheter will be positioned in the aorta for 3 minutes of stable BP waveforms recording. Intracoronary nitroglycerin will be administered at a dose of 300 µg. At the end of the coronary angiography, an additional 3 minutes of recording will be performed in the aorta.

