#### Standardized Measures in the Intensive Care Unit

The investigator will put the ring on the same arm of the arterial catheter for simultaneous measurements. Enrolled patients must have had an arterial catheter in place at the time of inclusion to the study. No arterial catheters were placed for the sole purpose of this study. Arterial catheterization will be performed by the intensive care team according to current medical guidelines.

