### Sample Size

The sample size is chosen based on the recommendations of the ISO 81060 guidelines [17] to determine the feasibility of noninvasive BP monitoring. Based on previous research, study sample size calculations for validation of BP measuring devices showed that 35 individuals is adequate for a high accuracy device (defined as mean BP difference between reference and test device measurement 0, SD 3-6 mmHg) [16]. Consensus was reached that studies performed on the general population should include adult participants; both individuals who are hypertensive and normotensive; ≥30% males and ≥30% females; ≥5% of the reference systolic BP readings ≤100 mmHg, ≥5% with ≥160 mmHg, and ≥20% with ≥140 mmHg; and ≥5% of reference diastolic BP readings ≤60 mmHg, ≥5% with ≥100 mmHg, and ≥20% with ≥85 mmHg. Due to the heterogenicity of patients to be included, we plan to enroll 25 patients in the cardiac catheterization laboratory and 10 patients in the ICU.

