### Statistical Methods

Categorical variables will be reported as counts and percentages; continuous variables will be reported as mean and SD or as median with 25% to 75% IQR according to their distribution as root mean square error. Normality will be assessed by visual inspection of histograms, the computation of Q-Q plots, and the Shapiro-Wilk test. Categorical variables will be compared using chi-square or Fisher exact test as appropriate. Continuous variables will be analyzed using the Student *t* test or the Wilcoxon rank sum test according to their distribution. Categorical variables fall into 3 groups representing the limit of the absolute BP differences: ≤5 mmHg, ≤10 mmHg, and ≤15 mmHg. Both arterial line and Senbiosys device signals will be segmented to epochs of duration (10-45 seconds). BP values will be computed for each epoch. Furthermore, for each epoch, we will compute the reliability index. Epochs with reliability indexes above a given threshold will be qualified for our study. Bland-Altman plots for repeated measures will be used to analyze SBP, DBP, and MBP data collected from the Senbiosys device and the arterial line [18]. Mean difference in scores (bias) and 95% limits of agreement, including the differences between noninvasive and invasive measurements (bias ± 1.96*SD), will be computed. Pearson correlation will be used to characterize the relation between noninvasive and invasive BP measurements. The acceptable bias and precision for arterial pressure measurements were fixed a priori at <5 and 8 mm Hg, respectively [16]. All statistical analyses will be performed using Matlab R2019a (MathWorks).

The null hypothesis is that the difference between invasive and noninvasive methods of BP calculated by Bland-Altman analysis are not within the clinically acceptable range.

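### One bias and one SD per pressure are judged against a single pair of limits, although the invasive reference is the aorta in 25 patients and an artery of the ring arm in 10

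*Protocol article*

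**What the plan says.** The two settings use different invasive references. In Standardized Measures in the Cardiac Catheterization Laboratory, both recordings are aortic: "At first, the catheter will be positioned in the aorta for 3 minutes of stable BP waveforms recording", and at the end of the angiography "an additional 3 minutes of recording will be performed in the aorta". In Standardized Measures in the Intensive Care Unit, "The investigator will put the ring on the same arm of the arterial catheter for simultaneous measurements". The ICU artery is not named; that it lies in the arm follows from this sentence.

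The outcome and the analysis do not carry that distinction. Outcomes defines, for each of SBP, DBP and MBP, a mean bias and an SD of the bias between invasive and noninvasive readings. Under Statistical Methods, "Bland-Altman plots for repeated measures will be used to analyze SBP, DBP, and MBP data collected from the Senbiosys device and the arterial line", with acceptance limits of <5 mmHg for bias and 8 mmHg for precision. Sample Size justifies 35 as a total and then sets the cath-lab and ICU numbers: "Due to the heterogenicity of patients to be included, we plan to enroll 25 patients in the cardiac catheterization laboratory and 10 patients". No section gives a result by setting or reference site, a site term in the analysis, or a conversion between aortic and arm pressure.

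**The concern.** Bias here means device minus reference, so it depends on which pressure serves as the reference. If aortic and arm pressures differ in the same patient, a device cannot be unbiased against both. A single bias over both groups then estimates a weighted average of two quantities, with weights set by the 25/10 recruitment split. The difference between the two also enters the single SD. Bland-Altman analysis for repeated measures deals with several readings per patient; it does not reconcile two reference sites.

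At stake is the accuracy verdict on the primary outcome. It could be favourable while one group is well outside the bias limit, or unfavourable for a device that is accurate against the pressure it is meant to estimate. The admitted heterogeneity of the patients is used only to set the numbers 25 and 10.

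**Working it through.** **Inputs from the protocol.** 25 aortic-reference and 10 arm-reference patients, and 25 + 10 = 35, which agrees with the stated total. Whether 35 is adequate cannot be re-derived, because no alpha or power is given; nothing below depends on it. Within-site SD is taken as 3 to 6 mmHg, the range in Sample Size: "35 individuals is adequate for a high accuracy device (defined as mean BP difference between reference and test device measurement 0, SD 3-6 mmHg". Limits: bias <5 mmHg and precision 8 mmHg, the latter read as the SD of the differences.

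**Assumed input.** d is the absolute difference between the two site-specific biases. The documents give no value, so 5, 10 and 15 mmHg are shown. d need not be the same for SBP, DBP and MBP.

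**Formulas** (equal weight per patient, one value per patient, p = 10/35 = 0.286):
- Pooled SD² = within-site SD² + p(1 − p)d² = within-site SD² + 0.204 d²
- Device unbiased against the aorta (ICU bias = d): pooled bias = 10d/35
- Device unbiased against the arm artery (cath-lab bias = d): pooled bias = 25d/35

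**Results** (mmHg, absolute values):

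| d | Pooled bias, unbiased vs aorta | Pooled bias, unbiased vs arm | Pooled SD, within 3 | Pooled SD, within 6 |
|---|---|---|---|---|
| 5 | 1.4 | 3.6 | 3.8 | 6.4 |
| 10 | 2.9 | 7.1 | 5.4 | 7.5 |
| 15 | 4.3 | 10.7 | 7.4 | 9.1 |

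For d = 10: 10 × 10/35 = 2.9; 25 × 10/35 = 7.1; √(9 + 20.4) = 5.4; √(36 + 20.4) = 7.5.

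**Where the verdict changes.**
- Pooled bias reaches 5 at d = 5 × 35/10 = 17.5 for a device unbiased against the aorta, but at d = 5 × 35/25 = 7 for one unbiased against the arm artery.
- Pooled SD exceeds 8 once d > √((64 − 36)/0.204) = 11.7 (within-site SD 6) or √((64 − 9)/0.204) = 16.4 (within-site SD 3), although each group's own SD is within the planned range.

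**Sampling check.** In a simulation of 25 + 10 patients with cath-lab bias 0 and ICU bias 10, the pooled estimates met both limits in about 100% of trials at within-site SD 3 and 71% at SD 6.

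**Precision by site** (1.96 × 6/√n, normal approximation): ±2.4 for n=25, ±3.7 for n=10, ±2.0 for n=35.

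**The case against.** The strongest reply is that the protocol never says it pools. Statistical Methods states no N and no setting, and an analysis plan that is not shown could present results by setting. That limits how firmly the point can be put. It does not remove it: the outcome, the acceptance limits and the justified N are each given once, across two reference sites, and which pressure the device is judged against belongs to the outcome definition.

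The size rests on an assumed d, and the direction on which pressure the algorithm tracks. At d = 10 the same pooled analysis passes one device and fails the other. This is a fair limit on any claim about what will happen, and it is also why the target pressure has to be named.

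Several stronger readings are tempting and are not supported:
- *Opposite errors in the two settings will cancel and pass.* With +7 (cath lab) and −7 (ICU), pooled bias is (25 × 7 − 10 × 7)/35 = 3.0. At within-site SD 3 the pooled SD is √(9 + 40) = 7.0 and the device passes. At SD 6 it is √(36 + 40) = 8.7, and the plan's own SD limit catches it.
- *Applying the limits within each setting cures the problem.* It does not. For a device that reads arm pressure correctly, the cath-lab bias would become the full d instead of 25d/35.
- *Longer ICU recordings dominate the result.* The 10-15 minutes is wear time for every patient, not ICU recording length, and no epoch weighting is stated. No share can be derived.
- *The inter-arm criterion* ("difference >20mmHg in systolic arterial pressure" excludes) *leaves the cath-lab reference mismatched to the ring arm.* An aortic catheter has no matching side, and restricting the inter-arm difference further would not remove an aorta-to-arm gap.

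**Conclusion.** The concern holds as a defect in how the primary result is defined. As the protocol reads, one bias and one SD per pressure combine an aortic and an arm-artery reference, and a single pair of limits is applied to the mixture. At an assumed d of 10 mmHg the pooled outcome is a pass (bias 2.9, SD 5.4-7.5) with an ICU bias of 10, or a fail (bias 7.1), depending only on which site the device is unbiased against.

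This rests on pooling as the natural but inferred reading, on equal patient weights, and on a d that the documents do not give; if d is small the effect is small. Reference site is also fully confounded with setting: every aortic reading is from the cath lab and every arm reading from the ICU. A difference between the groups therefore could not be assigned to anatomy rather than to type of patient. The documents do not support saying that the trial's verdict will be wrong, or in which direction.

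**What to change.** 1. Report bias, 95% CI, SD and limits of agreement by reference site (aorta, n=25; arm artery, n=10), for SBP, DBP and MBP.
2. State which reference pressure the device is meant to estimate, and therefore which of these results is judged against <5 and 8 mmHg.
3. Note beside the other stratum that its bias includes any aorta-to-arm gap and is not device error alone.
4. Keep the 35-patient figure as a descriptive summary and state whether patients or epochs are weighted equally.

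No new data are needed. The costs are wider intervals (the half-widths above) and two strata that each fall short of the 35 that Sample Size justifies, so the 10-patient ICU result in particular will be imprecise. The Results section reports that data collection was completed by the end of June 2021; if the change is made after the data were seen, it should be labelled post hoc.

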#### Standardized Measures in the Intensive Care Unit

The investigator will put the ring on the same arm of the arterial catheter for simultaneous measurements. Enrolled patients must have had an arterial catheter in place at the time of inclusion to the study. No arterial catheters were placed for the sole purpose of this study. Arterial catheterization will be performed by the intensive care team according to current medical guidelines.

### Outcomes

The primary outcome is the assessment of mean bias (95% CI or precision of bias) for SBP, diastolic BP (DBP), and mean BP (MBP) between invasive and noninvasive BP measurements. The standard deviation of the bias (95% limits of agreement) will be assessed for SBP, DBP, and MBP measurements.

The percentage of signal with artifact, therefore not useable, will be determined. In this regard, secondary outcomes include a reliability index (Qualification Index) for BP epochs and count of qualified epochs.

### Participant Timeline

The timeline for enrollment, intervention, and data collection is outlined in Table 1.

**Table 1 table1:** Timetable of patient enrollment and intervention and data collection.

Study schedule	Patient information and inclusion	Intervention period
Visit 1	0	1
Time	≥12h before procedure	0
Patient information	✓^a^	—^b^
Informed consent	✓	—
Baseline characteristics: age, gender, CVRF^c^, etc	✓	—
BP^d^ recordings	—	✓
Primary outcome	—	✓
Secondary outcome	—	✓
Safety outcome	—	✓

^a^This item is included.

^b^This item is not included.

^c^CVRF: cardiovascular risk factor.

^d^BP: blood pressure.

### Sample Size

The sample size is chosen based on the recommendations of the ISO 81060 guidelines [17] to determine the feasibility of noninvasive BP monitoring. Based on previous research, study sample size calculations for validation of BP measuring devices showed that 35 individuals is adequate for a high accuracy device (defined as mean BP difference between reference and test device measurement 0, SD 3-6 mmHg) [16]. Consensus was reached that studies performed on the general population should include adult participants; both individuals who are hypertensive and normotensive; ≥30% males and ≥30% females; ≥5% of the reference systolic BP readings ≤100 mmHg, ≥5% with ≥160 mmHg, and ≥20% with ≥140 mmHg; and ≥5% of reference diastolic BP readings ≤60 mmHg, ≥5% with ≥100 mmHg, and ≥20% with ≥85 mmHg. Due to the heterogenicity of patients to be included, we plan to enroll 25 patients in the cardiac catheterization laboratory and 10 patients in the ICU.

### Recruitment

Eligible participants will be identified via the principal investigator throughout the study period. The presence of exclusion criteria will be defined according to the patient’s clinician in charge. Patients’ capacity for discernment will be functionally assessed by the clinician in charge to determine whether the patient is capable of making a specific decision and whether the patient is capable of giving informed consent. If the eligibility criteria are met the patient will be formally enrolled. The written informed consent form will be signed by the patient and by one of the principal investigators. Only patients with the ability to provide consent in the ICU and the coronary care unit will be included.

Based on the current statistics for admissions to the ICU and cardiac catheterization laboratory in our institution, we estimate a total duration of 4 weeks for patient enrollment and the assessment of the primary and secondary end points.

### Data Collection

Patient characteristics and study outcomes will be transferred into an electronic case report form (REDcap Software, Vanderbilt University) designed to capture study information on the informatic structure of the HFR Fribourg. During the clinical trial, data will be accurately recorded, and the original documents will be stored at the clinical trials unit of the University and Hospital of Fribourg, under locked conditions when not in use.

### Statistical Methods

Categorical variables will be reported as counts and percentages; continuous variables will be reported as mean and SD or as median with 25% to 75% IQR according to their distribution as root mean square error. Normality will be assessed by visual inspection of histograms, the computation of Q-Q plots, and the Shapiro-Wilk test. Categorical variables will be compared using chi-square or Fisher exact test as appropriate. Continuous variables will be analyzed using the Student *t* test or the Wilcoxon rank sum test according to their distribution. Categorical variables fall into 3 groups representing the limit of the absolute BP differences: ≤5 mmHg, ≤10 mmHg, and ≤15 mmHg. Both arterial line and Senbiosys device signals will be segmented to epochs of duration (10-45 seconds). BP values will be computed for each epoch. Furthermore, for each epoch, we will compute the reliability index. Epochs with reliability indexes above a given threshold will be qualified for our study. Bland-Altman plots for repeated measures will be used to analyze SBP, DBP, and MBP data collected from the Senbiosys device and the arterial line [18]. Mean difference in scores (bias) and 95% limits of agreement, including the differences between noninvasive and invasive measurements (bias ± 1.96*SD), will be computed. Pearson correlation will be used to characterize the relation between noninvasive and invasive BP measurements. The acceptable bias and precision for arterial pressure measurements were fixed a priori at <5 and 8 mm Hg, respectively [16]. All statistical analyses will be performed using Matlab R2019a (MathWorks).

The null hypothesis is that the difference between invasive and noninvasive methods of BP calculated by Bland-Altman analysis are not within the clinically acceptable range.

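### The rank sum test and ordinary Pearson correlation named in the Statistical Methods do not suit paired device and arterial-line readings repeated within 35 patients; this mainly affects the supporting analyses

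*Protocol article*

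**What the plan says.** All of this is in the protocol article.

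- **Design** (Study Setting): one arm, with both methods recorded together: "The patients will undergo invasive BP estimation and will simultaneously wear the device".
- **Patients** (Sample Size): "we plan to enroll 25 patients in the cardiac catheterization laboratory and 10 patients in the ICU", 35 in all.
- **Unit of measurement** (Statistical Methods): both signals are cut into epochs of 10 to 45 seconds, with a pressure computed for each epoch.
- **Tests** (Statistical Methods): continuous variables are analysed by the Student t test or the "Wilcoxon rank sum test according to their distribution". The text does not say which variables or groups are compared, or whether the t test is paired.
- **Correlation** (Statistical Methods): "Pearson correlation will be used to characterize the relation between noninvasive and invasive BP measurements".
- **Agreement** (Statistical Methods): "Bland-Altman plots for repeated measures will be used to analyze SBP, DBP, and MBP data collected from the Senbiosys device and the arterial line", followed by bias and limits of agreement as bias ± 1.96 SD. The null hypothesis is framed in terms of the Bland-Altman analysis.
- **Primary outcome** (Outcomes): mean bias with its 95% CI for systolic, diastolic and mean pressure.

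**The concern.** The rank sum test compares two independent samples. In this trial every device value has a reference value from the same patient at the same moment, and each patient contributes many such pairs. No signed-rank, clustered or within-patient method is named for the tests or the correlation.

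Two things are at stake. First, a pooled correlation can look excellent merely because patients differ in their pressure level, even if the device misses every change within a patient. That matters for a device meant for continuous monitoring, and the cath-lab procedure records before and after a vasodilator, where within-patient change is of direct interest. Second, any device-versus-reference p-value or interval that counts epochs as independent would rest on hundreds of observations when only 35 patients supply the independent information.

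**Working it through.** The plan gives no figure of its own on this point; the 35 patients are not in dispute. Variance components are not in the documents, so those below are assumptions, with ranges.

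**1. Epochs per patient.** Cath lab: two 3-minute recordings = 360 s, so 360/45 = 8 to 360/10 = 36. ICU, taking the 10 to 15 minutes of wear as recording time: 600/45 ≈ 13 to 900/10 = 90. Total: 25×8 + 10×13 = 330 to 25×36 + 10×90 = 1,800, before unqualified epochs are dropped.

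**2. Pooled Pearson r.** Assume a pressure SD of 18 between and 5 within patients, and a device error SD of 5 between and 3.5 within patients (variance 25 + 12.25 = 37.25).

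- Reference variance: 324 + 25 = 349, of which 324/349 = 93% is between patients.
- Full within-patient tracking: r = √(349/(349 + 37.25)) = 0.95.
- No within-patient tracking: covariance 324, device variance 324 + 37.25 = 361.25, so r = 324/√(349×361.25) = 0.91.
- Range with no tracking:
  - SDs 10 between and 8 within: 100/√(164×137.25) = 0.67.
  - SDs 18 and 8: 324/√(388×361.25) = 0.87.
  - SDs 20 and 3: 400/√(409×437.25) = 0.95.

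So r barely separates a device that follows changes from one that does not, unless patients are similar in level or vary a good deal within the recording.

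**3. A CI that treats epochs as independent.** Take 25 patients × 12 epochs + 10 × 25 = 550 epochs, with the same error SDs.

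- Naive variance of the mean difference: 37.25/550 = 0.068.
- True variance: 25×(25×12² + 10×25²)/550² + 12.25/550 = 25×9,850/302,500 + 0.022 = 0.836.
- Coverage: 2Φ(1.96×√(0.068/0.836)) − 1 ≈ 42%.
- If the device does not track, the within-patient difference variance is 12.25 + 25 = 37.25. The naive variance is 62.25/550 = 0.113 and the true variance 0.814 + 0.068 = 0.882, giving coverage of about 52%.

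Simulation gives about 42 to 53%, and 95% from patient means. With other assumptions (total difference SD 6, ICC 0.3 to 0.8), simulated coverage runs from 70% down to 48% with the fewest epochs and from 33% down to 21% with the most. The design effect 1 + (m − 1)×ICC runs from 1 + 7×0.3 = 3.1 to 1 + 89×0.8 = 72.2, so such intervals are too narrow by a factor of √3.1 ≈ 1.8 to √72.2 ≈ 8.5.

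**4. Rank sum on device versus reference, true bias 5 mmHg, setting of step 3.** On patient means it detects the bias in under 1% of simulated trials, against about 100% for signed-rank. On epochs it detects it in over 99%. With no bias, epoch-level unpaired t and rank sum tests reject in 0 to 1% of trials (few epochs) or 4 to 20% (many), instead of 5%; this uses the total SD of 6 with pressure SDs of 20 and 5. The test is thus miscalibrated, in a direction that depends on how it is run.

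**5. Pairing alone is not enough.** Paired tests run on epochs have a simulated type I error of 30 to 79%; on patient means it is 4 to 6%.

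**The case against.** The strongest defence is that the primary analysis is already right. Repeated-measures Bland-Altman is a paired-difference method for clustered data, and the null hypothesis is tied to it. This stands. A reader might infer from bias ± 1.96 SD that the primary CI will count epochs as independent. The text leaves the SD unspecified but does not say that, and the formula may sit in a fuller document.

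It can also be said that the t and rank sum sentence never names device versus reference, that Student t may be paired, and that the two patient groups are a legitimate use for both tests. This stands in part. However, no cath-lab versus ICU comparison is planned in the article, and the sentence that follows defines the categorical variables by absolute device-reference differences. The target of the tests is therefore undefined, and at least part of that paragraph concerns agreement data.

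Two stronger readings are tempting. One is that the unpaired test would clear a biased device: step 4 shows this for patient means but not for epochs, and the text does not fix which is used. The other is that a non-significant difference would be read as agreement: nothing says so, and acceptability is judged against limits of 5 and 8 mmHg.

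Finally, Pearson is described as characterising a relation; it is computed on pairs, and no decision rests on it. That is fair, but a descriptive r can still mislead, as step 2 shows.

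**Conclusion.** The point holds for the supporting analyses. The correlation is the clearest part, because the text applies it explicitly to device and arterial-line pressures: about 0.91 with no within-patient tracking under the central assumptions, and 0.67 to 0.95 over the range shown. The rank sum test is unsuitable if used for device versus reference, which the text neither states nor excludes. Any p-value or CI that treats epochs as independent would be invalid: coverage is about 42 to 53% in the central setting and 21 to 70% over the wider one. These sizes rest on assumed variance components and on the epoch counts in step 1; the direction does not. The planned Bland-Altman analysis of bias and limits of agreement is not shown to be wrong. It would gain from one sentence on the variance behind its CI.

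**What to change.** Amend the Statistical Methods as follows.

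1. State what the tests compare. Restrict rank sum and unpaired t to comparisons between cath-lab and ICU patients.
2. For any device-versus-reference test, use one mean difference per patient with a paired t or Wilcoxon signed-rank test, or a linear mixed model of epoch differences with a random patient effect.
3. State that the 95% CI of the bias uses the same patient-level variance as the repeated-measures Bland-Altman analysis.
4. Replace the pooled Pearson r by separate between-patient and within-patient (repeated-measures) correlations.

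The cost is wording and minor programming, with no new data. The downside is wider intervals than an epoch-level calculation would give, and probably a less favourable correlation.
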